### Secondary outcome measures

#### Nutritional status

##### The scored Patient-Generated Subjective Global Assessment (PG-SGA©)

The scored PG-SGA© consists of two sections with seven domains. The first section, which will be completed by the participant, is in the form of a checklist and comprised weight, food intake, symptoms, activities, and function. The second section will be completed by the researcher as it covers the disease and its relation to nutritional requirements, and determination of metabolic demands, and will be followed by a nutrition-related physical examination, including subjective body composition (i.e., fat, muscle, and fluid status).

A score ranging from 0 to 4 will be given for each domain depending on the impact on the nutritional status. PG-SGA© scores that range from 0 to 35 reflect a greater risk of malnutrition or indicate a lower nutritional status of the patient. These scores will be transformed into global ratings—Stage A, Stage B, and Stage C—which will represent the states of being well-nourished, moderately malnourished, and severely malnourished, respectively. Then, the criticality of the need for nutritional intervention will be identified and classified based on the scores with 0 to 1 point for those requiring no intervention, health education for 2 to 3 points, dietetic intervention for 4 to 8 points, and nutrition support for ≥9 points.

##### Anthropometric measurements

The anthropometric measurements will be carried out in this study including body weight, height, mid-arm circumference (MAC), and triceps skinfold thickness (TSF). These measurements will be taken directly before the interview with all the participants.

Body weight and height measurements will be taken while participants are barefooted and wearing lightweight clothing with empty pockets, without watches, or other accessories. Weight will be determined to the nearest 0.1 kg using a digital weighing scale (SECA, British Indicators Ltd., UK). The machine will be calibrated every morning with a standard weight before it is used. Height will be measured in the standing position to the nearest 0.1 cm using a SECA 206 microtoise tape (Vogel and Halke GmbH & Co, Hamburg, Germany) which will be attached to the wall. The participant will be asked to stand straight with their head in the Frankfort plane, feet together, knees straight, and heels, buttocks, and shoulder blades in contact with the vertical surface of the wall.

MAC and TSF will be taken without any sleeve on the measuring arm, watches, or other accessories. The subject will be in a relaxed standing position with the arms hanging by the sides. MAC will be measured in the middle arm (same distance) from acromiole and radiale bone, to the nearest 0.1 cm using SECA 201 circumference measuring tape (SECA, British Indicators Ltd., UK). Meanwhile, TSF will be measured at the most posterior part of the triceps when viewed from the side at MAC level, to the nearest 0.1 mm using a Harpenden skinfold caliper (HaB International Ltd, UK). The caliper will be calibrated every morning before it is used to minimize measurement errors. All anthropometric measurements will be taken twice by the same investigators, and the average will be used. The weight and height of the participants will then be used to calculate the BMI [24].

##### Biochemical data

Data on serum albumin, white blood count (WBC), and hemoglobin level will be obtained from the patient’s medical report at baseline and at the end of the visit. For other blood parameters, 10 ml of venous blood will be taken following an overnight fast. The samples will be separated immediately using centrifugation (1800*g* for 10 min at 4°C). The serum will be stored at 80°C until analysis for the measurement of C-reactive protein, which will be performed after all samples are collected.

##### Dietary intake

Dietary intake will be measured through a 24-h dietary recall at baseline and 2 days of 24-h dietary records during visits 2 and 3. The participants will be required to keep a record of all food and beverage intakes within every 24 h of data collection. The participant will be asked about their intake before the visit. Details of food information and descriptions, which include brand names, preparation, and cooking methods, as well as recipes of any mixed dishes eaten during the study period, will also need to be recorded. In situations where any foods and beverages are consumed away from home, the participants will be encouraged to describe the quantities consumed using the household measurements as well (e.g., glass, cup, Chinese rice bowl, plate, tablespoon, and teaspoon).

The researcher will explain to both groups how to record their 2-day intake in a food diary. They will also be given a detailed set of instructions together with a food album. The food album lists commonly consumed food and includes details of portion sizes relative to typical household measurements to facilitate recalls of serving size and improved accuracy.

A computerized local dietary analysis program, Nutritionist Pro version 2.0 (First Data Bank, The Hearst Corp. USA) will be used to analyze the nutrient intakes of the patients. The foods and beverages consumed by the participants will be coded by type and amount which then will be analyzed for nutrient content primarily based on the Malaysian Food Composition Database [25]. Nutritionist Pro will then be used to calculate dietary intake at baseline (based on one 24-h dietary recall), and at other subsequent assessment time points (based on average intake over every 2 days of dietary record).

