### Data collection procedure

Each participant will be assessed in the clinic/wards during four different sessions (baseline, first, second, and third visits) over the study period (Fig. 2). During the baseline visit, screening and recruitment will be conducted at the surgical clinic, attended by potential participants who have appointments for examination and are in line to get surgery appointments. Potential participants are those who are scheduled to have surgery and meet the inclusion and exclusion criteria. The scheduled project team member will be assigned to approach and inform all potential participants about the study procedures. The patient information sheet and consent form will be given to eligible subjects who have agreed to be recruited for the study. Subjects are allowed to bring back the consent form if they are keen to seek advice from their family members. Agreed and consented participants will be randomly sampled and divided into two (2) groups.

During the baseline visit (pre-study phase), the researcher will be obtaining the patients’ history of dietary intake via 24-h dietary recall. Based on this assessment, the researcher will be able to determine participants’ estimated intake based on their estimated requirements. The dietary advice will be given individually and is structured based on ESPEN guidelines for surgical patients [15].

Participants who are allocated to Group SS will be supplied with ONS, a maximum of 4 servings/day according to their requirements. Participants need to consume the supplied ONS starting from recruitment until 6 h before surgery. Follow-up through phone calls from time to time will be done to assess participants’ compliance with the supplied ONS. During the study phase, participants need to consume ONS once allowed, and compliance will be assessed daily until discharge. Participants will be asked to keep the ONS packaging material during both phases. The researcher will collect the packaging material during the 1st visit and the day of hospital discharge. While Group NN will not be supplemented by any of ONS in the pre-study phase and study phase.

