During visits 1, and visit 3, dietary intake data will be collected using a self-administered 2-day 24-h dietary record. All the participants will also be given comprehensive verbal instructions on the method of recording food intake using the 2-day 24-h dietary record. The illiterate participants will be asked to seek assistance from their family members to record for them. They will be asked to complete the 2-day 24-h dietary record of food intake before their next visit, which will be used as the basis for their individualized dietary advice.

During the baseline visit, all data collection will be conducted including a socio-demographic questionnaire, with exception of data for *length of hospital stay* which can only be obtained at visit 2. Meanwhile, anthropometric measurements (except height) and PG-SGA questionnaire, the same methods and instruments will be used repeatedly at visit 1 and visit 3. Data for handgrip will be conducted at every visit while biochemical data will be collected for a second time at the end of the study which is during visit 3. The details of the assessment and procedure are shown in Table 3.

**Table 3 Tab3:** The assessment procedure at (baseline), visit 1, visit 2, and visit 3

The assessment procedure	Visit			
	Baseline	1	2	3

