### Analysis of results

The data collected will be analyzed by using the statistical software Statistical Package for Social Sciences (SPSS) and checked for normality via Kolmogorov-Smirnov analysis. All data will be normally distributed as indicated by *p*>0.05 unless otherwise stated. If the data will be not normally distributed, analyses will be carried out on the natural logarithm of the values to improve the symmetry and homoscedasticity of the distribution.

Descriptive statistics, including percentages, mean values, and standard deviations, will be used to describe the baseline demographic data, type of diseases, nutritional status level including anthropometric data, and dietary intake. The median will be used when the data are skewed. When the data become skewed, the mean loses its ability to provide the best central location for the data because the skewed data are dragging it away from the typical values. In addition, the median is not strongly influenced by skewed values.

The values from both groups will be compared using an ANOVA test for approximately normally distributed data, followed by tests on pairs of groups using the Bonferroni adjustment. Non-normal data will be compared by the Kruskal-Wallis test followed by the Mann-Whitney *U* test. ANCOVA or logistic regression will be used with models adjusted according to potential confounders to determine predictors of changes in the key outcome variables of the length of hospital stay with *p*<0.05 significance level. An intent-to-treat (ITT) analysis will be performed to determine the effect of the intervention study on the assumption that participants have adhered to the dietary advice and ONS at the start of the intervention study and had baseline and endpoint values. In other words, ITT analysis includes every randomized subject; according to randomized treatment assignment regardless of their non-compliance, subsequent withdrawal from treatment, or deviation from the protocol and anything that happens after randomization. The effect of intervention between treatment groups on outcome parameters will be carried out by using General Linear Model (GLM) for repeated measure procedure. This method is quite robust to violation of the assumption of normality [33].

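### Dietary intake: a one-day recall at baseline and two-day records later make baseline a poor time level in the repeated-measures model; it serves better as a covariate

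*Protocol article*

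**What the plan says.** All references are to the protocol article.

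- **Instruments.** Under Dietary intake, the measure is "a 24-h dietary recall at baseline and 2 days of 24-h dietary records during visits 2 and 3". Baseline intake is calculated "based on one 24-h dietary recall", and later values are averages over two recorded days. Table 3 agrees.
- **Mode.** Data collection procedure says of the baseline visit that "the researcher will be obtaining the patients’ history of dietary intake via 24-h dietary recall". Of the later visits it says that "dietary intake data will be collected using a self-administered 2-day 24-h dietary record". The interviewer, the mode and the number of days therefore all change together after baseline.
- **Visits.** That same section places the records at visits 1 and 3. Dietary intake and Table 3 place them at visits 2 and 3.
- **Analysis.** Analysis of results states: "The effect of intervention between treatment groups on outcome parameters will be carried out by using General Linear Model (GLM) for repeated measure procedure". It does not say whether baseline is a level of the time factor or a covariate. ANCOVA is named there only in connection with length of stay.

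**The concern.** If baseline is the first time level, two things follow.

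First, the time effect and each arm's own change from baseline combine three things: true change in intake, the effect of surgery and hospital feeding, and the switch from a researcher-led recall to a self-kept record. They cannot be separated. A rise or fall in intake within an arm would have no clear meaning.

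Second, the baseline value carries twice the day-to-day variance of a two-day mean. A group-by-time contrast subtracts that value and takes on its noise. With 68 patients randomised, and about 54 left after the planned 20% drop-out (68 × 0.8 = 54.4), that loss of precision matters for an outcome that shows whether the intervention raised intake at all.

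**Working it through.** **How baseline enters the model.** The role of baseline is inferred from four places:

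- The Abstract describes the additional outcomes as changes in biochemical, nutritional and functional status.
- Analysis of results refers to participants with both baseline and endpoint values, and the effect-size paragraph that follows speaks of the size of changes.
- One model sentence covers all outcome parameters. In Table 3 the biochemical outcomes are measured only at baseline and visit 3, so for them a repeated-measures procedure is possible only with baseline as a level.
- No covariate is named for intake.

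**Precision: inputs.** The article gives no variance or power figure for intake, so there is none to reproduce. The following are assumptions: between-person variance 1 at each time; day-to-day variance L, equal for both instruments and independent between days; correlation r of true intake between baseline and follow-up. I take L from 1 to 2 and r from 0.4 to 0.8.

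**Formulas, for one follow-up visit.**

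- Var(baseline, one day) = 1 + L
- Var(follow-up, two-day mean) = 1 + L/2
- Covariance = r
- Change from baseline: (1 + L) + (1 + L/2) − 2r
- Baseline as covariate: (1 + L/2) − r²/(1 + L)
- Follow-up only: 1 + L/2

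| L | r | Change | Covariate | Follow-up only | Change ÷ covariate | Saving of covariate over follow-up only |
|---|---|---|---|---|---|---|
| 1 | 0.4 | 2.70 | 1.42 | 1.50 | 1.90 | 5% |
| 1 | 0.8 | 1.90 | 1.18 | 1.50 | 1.61 | 21% |
| 2 | 0.4 | 4.20 | 1.95 | 2.00 | 2.16 | 3% |
| 2 | 0.8 | 3.40 | 1.79 | 2.00 | 1.90 | 11% |

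The change analysis thus uses 1/2.16 = 46% to 1/1.61 = 62% of the information that the covariate analysis uses. At L = 2, r = 0.4, dropping baseline as a response accounts for (4.20 − 2.00)/(4.20 − 1.95) = 98% of the gain. At L = 1, r = 0.8 it accounts for (1.90 − 1.50)/(1.90 − 1.18) = 56%. Over a wider range (L 0.5 to 3, r 0 to 0.9) the covariate variance is 25 to 62% below the change variance.

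**Power by simulation.** With 34 per arm, L = 1, r = 0.6 and a true difference of 0.8 between-person SD, power was 0.93 with the covariate (mean of the two follow-up visits), 0.66 for the change score, 0.60 for the group main effect with baseline as a level, and 0.55 for the group-by-time test.

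**Confounding by simulation.** There was no treatment effect and no true change, but records read 0.5 between-person SD below recall in both arms (27 or 34 per arm).

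- Between-arm tests kept their level: group-by-time 0.044 to 0.055, change score 0.040 to 0.059, covariate model 0.045 to 0.062.
- The control arm's own change was significant in 27 to 61% of runs.

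When records read 15% low in proportion, a true difference of 0.80 became about 0.68 (0.85 × 0.80) under both the change score and the covariate model.

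**The case against.** The strongest reply is that the article never makes baseline a time level. A repeated-measures general linear model accepts covariates, so the analysis proposed here already fits the wording, and the choice of response levels for one secondary outcome is usually left to an analysis plan that is not shown. It stands that this is an inference. It does not dispose of the point, because the article itself fixes both the mismatched instruments and the single model, and its references to change and the biochemical schedule point one way.

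A reader might infer that the switch of instrument biases the treatment comparison. The documents do not support that. Both arms use the same instruments at the same visits, the planned question is the effect between groups, and a common shift left the between-arm error rates near 5%.

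A reader might also infer that the covariate cures the confounding of time with instrument. It does not; it only stops estimating change from baseline. Proportional reporting error remains, as does error that differs by arm, which is possible because the intervention arm receives more intensive counselling.

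Nor is the change free. It uses a degree of freedom, worth about 2% in variance at 54 patients. The correlation between the measured baseline and follow-up must exceed about 0.14 to break even. At L = 2, r = 0.4 that correlation is 0.4/√(3 × 2) = 0.16, so the covariate then gains almost nothing over follow-up only.

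**Conclusion.** The point holds as one of precision and interpretation, for a secondary outcome; length of stay is untouched. On the natural reading that baseline is a time level, the variance of change from baseline is 1.6 to 2.2 times the covariate-adjusted variance, and change within an arm cannot be read as change in intake. The size rests on assumed values of L and r and on a change score as comparator, since the article gives no dietary variances. The benefit comes mainly from taking the one-day recall out of the response. The covariate adds 3 to 21% over follow-up only, before the lost degree of freedom.

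Two matters limit use of the recall as a covariate. Data collection procedure describes it after the allocation step, and Recruitment says the investigator knows the allocation. A recall led by someone who knows the arm is not a safe baseline in either analysis. The visits at which the records are taken are also inconsistent, and must be known before the outcome can be defined.

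**What to change.** 1. Reconcile Data collection procedure (records at visits 1 and 3) with Dietary intake and Table 3 (visits 2 and 3).
2. Confirm that the baseline recall was taken before allocation was known. If it was not, do not use it as a covariate; analyse the post-baseline records alone.
3. State the model: for energy and protein intake, the post-baseline two-day records are the repeated outcomes, with arm, visit and arm-by-visit terms and the baseline recall as a covariate.
4. State that change from baseline in intake will not be interpreted within arms, because the instruments differ, and that the covariate does not remove proportional or arm-specific reporting error.
5. Give a rule for participants without a baseline recall, so that they are not lost from the analysis by default.

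Trial status reports recruitment complete on 31 December 2021, so matching the baseline instrument to the later ones is presumably no longer possible. The change needs no new data. It costs a few lines of analysis wording, one degree of freedom, the estimate of change from baseline, and the missing-recall rule.

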##### Handgrip strength

Handgrip strength is measured on the non-dominant hand using a Jamar hand dynamometer (Fred Sammons Inc, Burr Ridge, Illinois, USA). Handgrip strength as a surrogate marker for muscle strength in patients with cancer has been well documented elsewhere. Subjects will be sitting with their shoulder adducted and neutrally rotated, elbow flexed at 90°, forearm in the neutral position, and standard verbal instructions will be given to the subjects to squeeze the dynamometer as hard as possible for three times after an interval of 5 s in between grips. An average of three successive attempts will be used as the final result.

### Other variables

#### Participant details and demographics

Information on the participants’ address, contact number, date of birth, age, sex, ethnic group, education level, job status, income level, and marital status will be recorded.

#### Medical history

Investigation of participants’ medical history on the type of disease, duration, treatment obtained, and medication received.

### Statistical analysis

#### Sample size calculation

A systemic review study in 2016 showed that early feeding has a significantly shorter length of hospital stay (*p*<0.01) compared to the late timing of feeding with a difference of −1.72 days and not associated with an increase in clinically relevant complications [26]. Several other studies also support early nutrition for surgery patients significantly shortening the length of hospital stay [27–29].

LOS was chosen to calculate the sample size because it has been used widely as a primary outcome in most nutrition-related RCT studies [30–32] among patients undergoing surgery. The sample size was calculated based on the data from a study conducted on colorectal cancer patients undergoing surgery [30]. The primary outcome was calculated based on the difference in LOS between two groups (control and intervention group) which was 3.45 days.

A large effect size of 0.8 for clinical significance was assumed, and practicality for this research was considered, with a power (*β*) of 90% and a probability (*α*) of 0.05. Allowing for a “drop-out” rate of 20% for the RCT study, we aim to recruit participants who will be included in each group, with the final sample size calculated as 68 participants with 34 participants in each group, respectively.

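### For the two-sided tests planned, 34 per group gives 90% power only with no loss; after the stated 20% drop-out it is about 82%

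*Protocol article*

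**What the plan says.** The section on sample size calculation in the protocol article bases the trial's size on length of hospital stay, the primary outcome. It takes a difference from an earlier study of colorectal cancer surgery, "the difference in LOS between two groups (control and intervention group) which was 3.45 days", and then states: "A large effect size of 0.8 for clinical significance was assumed, and practicality for this research was considered". The error rates follow: "with a power (*β*) of 90% and a probability (*α*) of 0.05". The text says that it allows for a drop-out "rate of 20% for the RCT study", and it ends "with the final sample size calculated as 68 participants with 34 participants in each group, respectively". It gives no standard deviation, no sidedness and no number before drop-out.

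The section on analysis of results sets out the group comparison: "The values from both groups will be compared using an ANOVA test for approximately normally distributed data". Non-normal data go to Kruskal-Wallis and Mann-Whitney tests. ANCOVA (or logistic regression) and a repeated-measures general linear model are also planned, and 0.05 is the significance level. No directional test is mentioned anywhere.

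**The concern.** An effect of 0.8 with 90% power and a two-sided 5% test is a familiar combination, and it calls for 34 patients per group with data. That is the same number the protocol calls final after a 20% drop-out allowance. A figure cannot be both the requirement before loss and the requirement after it, unless the calculation used something other than a two-sided 5% test.

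At stake is the power claimed for the primary outcome. If length of stay shows no significant difference, readers will weigh that result against a stated type II error of 10%. Under the protocol's own loss assumption and its own planned tests, that error can be about 18%.

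**Working it through.** **Inputs.** From the sample size section: d = 0.8, power 0.90, alpha 0.05, drop-out 20%, 1:1 allocation, 34 per group. Sidedness is not stated there. The ANOVA F test and the Kruskal-Wallis test in the analysis section are non-directional, so the planned two-group comparison corresponds to a two-sided 5% test.

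**Step 1: two-sided requirement before drop-out.**
- Normal approximation: n = 2(1.960 + 1.282)²/0.8² = 2 × 10.507/0.64 = 32.84, so 33 per group.
- Exact (noncentral t): n = 33.83, so 34 per group. Power at 34 is 90.2%.

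The protocol's final number is therefore the two-sided t-test number with nothing added.

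**Step 2: two-sided requirement with 20% loss, n/(1 − 0.2).**
- Normal: 33/0.8 = 41.25, so 42 per group, 84 in total.
- t test: 34/0.8 = 42.5, so 43 per group, 86 in total.

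**Step 3: can 68 be reached with the drop-out included?** Yes, with a one-sided alpha of 0.05.
- Normal: n = 2(1.645 + 1.282)²/0.64 = 2 × 8.564/0.64 = 26.76, so 27. Then 27/0.8 = 33.75, so 34 per group, 68 in total.
- t test: n = 27.47, so 28. Proper inflation gives 28/0.8 = 35 per group (70 in total). The shortcut of multiplying by 1.2 gives 28 × 1.2 = 33.6, so 34.

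An 80% power target does not explain 68: two-sided with drop-out it gives 25/0.8 = 31.25, so 32 per group (64), or 26/0.8 = 32.5, so 33 per group (66).

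**Step 4: power with 34 randomised per group and 20% lost.** 34 × 0.8 = 27.2, so 27 per group remain.

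| Evaluable per group | Two-sided power, t | Two-sided power, normal | One-sided power, t |
|---|---|---|---|
| 34 | 90.2% | 91.0% | 94.7% |
| 31 | 87.3% | not needed | 92.9% |
| 27 | 82.2% | 83.6% | 89.5% |

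With 27 per group the two-sided type II error is 100% − 82.2% = 17.8%, against the stated 10%.

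**The case against.** The strongest reply is that every stated figure can be reproduced together. A one-sided 5% normal approximation with correct inflation gives exactly 34 per group, and with 27 completers its power is about 90%. This stands. A reader might infer from Step 1 that the sample contains no drop-out allowance at all. The document does not establish that, because without sidedness or a number before drop-out nobody can tell which route was taken. But the one-sided route does not rescue the power statement: the protocol declares no one-sided test and plans non-directional ones.

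A second reply is that drop-out need not mean missing length of stay. Stay is fixed at discharge, whereas follow-up runs to four weeks afterwards, and the intent-to-treat paragraph says every randomised patient is included. This stands in part, and it makes 82% the lower end of a range. Yet the withdrawal criteria include patients who never have a qualifying operation, for whom no postoperative stay exists. The same intent-to-treat paragraph also speaks of participants having baseline and endpoint values. Some loss of the primary outcome is therefore to be expected.

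A third temptation is to go further: divide 3.45 days by 0.8 to get an SD of about 4.31 days, and then quote low power at the 1.72-day difference cited in the same section. The documents do not support this as fact. They give no SD, the 0.8 is described only as an assumed large effect, and the 1.72 days comes from a review of early against late feeding, cited as background. None of it bears on the drop-out question.

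**Conclusion.** The stated 90% power, the 20% drop-out allowance and 68 patients cannot all hold for the two-sided tests that the protocol plans. Either the inflation was omitted or it rests on an unstated one-sided alpha that the planned tests do not share. The consequence is the same on both branches: two-sided power at d = 0.8 is about 82% (84% by normal approximation) if the full 20% provide no length-of-stay data. It rises towards 90% as more drop-outs keep that outcome, for example 87% with 31 evaluable per group. Keeping 90% after the full loss would have needed 84 to 86 patients.

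These figures assume a two-sample comparison of means at two-sided 5%, equal loss in both groups, and the protocol's own effect of 0.8. The trial remains reasonably powered for that effect; the error lies in the power figure claimed.

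**What to change.** In the sample size section:

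- State that the test is two-sided at 5%.
- Say that 34 evaluable patients per group give 90% power at d = 0.8.
- Say that with 34 randomised per group and 20% without length-of-stay data, 27 per group remain and power is about 82%.
- Remove or correct the claim that 68 allows for 20% drop-out at 90% power.
- If the calculation was in fact one-sided, say so, give the number before drop-out, and still report the two-sided power, since that is what the planned tests deliver.

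Do not add an SD of 4.31 days or a power at 1.72 days as protocol facts.

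The cost is wording only. The protocol reports recruitment as completed, so no extra patients are asked for; the price is a less favourable stated power.
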